### Cerebral microdialysis

Patients will be monitored with cerebral microdialysis as part of standard patient care and according to local protocols.^24^ This will start immediately after injury and continue until clinically indicated (normally 5–7 days). The 100 kD cut-off MDialysis AB microdialysis catheters will be surgically implanted through a burr hole in white matter regions that appear normal on CT (mainly in the right, non-dominant frontal lobe). In patients with frontal contusions, catheters will be placed distant to intracerebral lesions. A standard 2 mm non-contrast brain CT scan will be taken within 24 hours to verify correct catheter placement. CT scan images will be coregistered with MRI.

Colloids such as dextran or albumin solutions will be added to the standard perfusion fluid to increase both fluid and protein recovery, as indicated by the manufacturer, and as recently reported.^25^ A standard flow rate of 0.3 µL/min will be used in all patients, allowing hourly recovery of brain extracellular fluid (about 20 µL). A subset of samples will be routinely analysed for lactate, pyruvate, glycerol, glutamate and glucose at bedside using a portable analyser (Iscus Flex, MDialysis AB, Stockholm, Sweden) to measure in vivo changes of cerebral metabolites. These data will be displayed real time for clinical use as indicated by published guidelines (16). Six vials (four hourly during collection) will be immediately frozen and stored after collection for the measurement of biomarker concentrations (eg, tau and NFL). These samples will be centralised to UCL laboratory.

Microdialysis and brain physiology data, including mean arterial pressure, intracranial pressure, cerebral perfusion pressure and core temperature, will be continuously recorded as part of a multimodal monitoring system and transferred to excel sheets. Additional information, including lab and arterial blood gas analysis data, hourly vital signs and ventilation parameters, if applicable, will be recorded.

### Sample size

The primary outcome measures are (1) change in diffusion tensor MRI measures over time (time frame: 10 days to 6 weeks, 6 months and 12 months), measured using fractional anisotropy (FA); (2) brain atrophy rates (time frame: 10 days to 6 weeks, 6 months and 12 months), using Jacobian determinant (JD) atrophy rates; (3) Change in levels of fluid biomarkers in blood (time frame: 0–5 days, 5–10 days, 10 days to 6 weeks, 6 months and 12 months) (4) Change in levels of fluid biomarkers in cerebral fluid (time frame: 48 hours to 7 days).

We estimate that a minimum of 140 patients will be necessary to test the contribution of DTI to prognostic modelling (type 1 error=0.05, power=0.95). Lost to follow-up is an important but unpredictable element and we have allowed for up to a further 25%–30% lost to follow-up by aiming to enrol 250 patients in the study. Our estimates indicated that a minimum of 12 imaging controls will be necessary for each centre.

To assess atrophy progression after TBI in work package two, our calculations indicate a sample size of 10 per group is needed to detect a group difference in brain atrophy over 6 months with effect size of f=0.32, assuming 95% and a correlation between repeated measures=0.9. Longitudinal brain atrophy rates will be calculated using the JD measure of atrophy rate generated using SPM 12 (UCL).^26^

Preliminary data suggest that moderate-to-severe TBI induces large changes in blood biomarker concentrations (eg, S100B, NFL). We estimate that the numbers required to show between group differences and relationships to outcome will be smaller than for DTI (1) or brain atrophy rates (2), on whose measures the study is primarily powered.

We have based the WP3 sample size (n=40) on previous similar microdialysis studies that have used 15–20 subjects and shown correlations between biomarker and imaging measures. With a sample size of 40 we should be adequately powered for this analysis, as well as being able to take into account the additional variability related to different centres.

### Statistical analysis plan

#### Fluid biomarkers

Blood biomarker trends will be described and compared between groups, as well as within individuals longitudinally. Distributions of variables will be assessed for normality and parametric/non-parametric tests used as needed for comparisons, with paired tests used within subjects for repeated measures. The relationship between fluid biomarkers and neuroimaging markers will be assessed, according to previously used approaches.^27^ We will use linear regression to look at the relationship between blood biomarker levels and continuous outcomes, or logistic regression for binarised outcomes such favourable/unfavourable recovery on the Glasgow Outcome Scale-Extended (GOSE) at 6 or 12 months. Cerebral microdialysis marker levels will be described over time and cross-compared to blood biomarker results, neuroimaging markers of axonal injury such as fractional anisotropy, and clinical outcomes, per Magnoni *et al*^16^

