Fluid biomarkers provide a complementary measure of axonal injury after TBI. Damage to neurons and glial cells can lead to increases in fluid biomarkers that are clinically informative.^10–12^ For example, cytoskeletal proteins are released from damaged axons and can be detected in the blood.^13 14^ Recent advances have identified a number of promising biomarkers with markedly increased sensitivity making it feasible to investigate and validate a blood biomarker of axonal injury.^15^ In this study, we will investigate the relationship between plasma and neuroimaging markers of axonal injury following TBI to determine whether a blood biomarker of axonal injury is valid and also study the time course of cognitive changes after TBI and their relationship to underlying brain injury.

Cerebral microdialysis can provide particularly important insights into the origin of biomarkers for axonal injury. Cytoskeletal proteins from damaged axons are released into the cerebral interstitial fluid compartment during acute axonal injury, from where they can be directly sampled.^16 17^ This can be achieved with high temporal resolution, providing a method for assessing the effects of therapeutic interventions.^18^ Recent findings indicate that microdialysis-based measurement of tau and neurofilament light (NFL) in the brain extracellular space may be a useful way to assess the severity of axonal injury in the acute setting. High initial microdialysis levels of tau are correlated with worse clinical outcomes.^16^ In addition, microdialysis concentrations of tau are proportional to abnormalities in diffusion tensor MRI, indicating that both measures reflect the same underlying axonal injury.^17^ In contrast, the relationship between local NFL concentrations and axonal injury has yet not been explored, although our preliminary data indicate that brain extracellular levels of NFL remain elevated for a longer period than tau and show heterogeneous dynamics that may reflect the progression of underlying axonal injury.

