### Structure of assessments

The study is organised into separate work packages, reflecting differing longitudinal assessment programmes for those at recruiting sites (table 2), as set-out in ‘goals and objectives’.

**Table 2 T2:** Work packages in participating major trauma centres

Institution	City	Country	Work package
Careggi University Hospital	Florence	Italy	1
Lausanne University Hospital	Lausanne	Switzerland	3
Niguarda Hospital	Milan	Italy	1
Policlinico of Milan	Milan	Italy	2
Santa Chiara Hospital	Trento	Italy	1
St Mary’s Hospital	London	UK	2
St George’s University Hospital	London	UK	2
University Medical Centre	Ljubljana	Slovenia	1

Patients participating in work package 1 will have clinical and demographic information collected acutely using the electronic case report form (eCRF). Blood samples will be collected twice in the first 10 days after injury, and at subsequent visits at 10 days – 6 weeks, and around 12 months. Standard MRI scanning will be performed at 10 days to 6 weeks only. Outcomes will be assessed at 6 months via telephone and 12 months via a face-to-face assessment. If face-to-face follow-ups are not possible then remote follow-up will be attempted for example, through telephone consultation.

Work package 2 comprises a more detailed programme of assessment. As per WP1, the eCRF will be completed acutely alongside blood tests twice in the first 10 days after injury. Advanced MRI will be performed at the 10 days to 6 weeks study visit, alongside blood biomarker assessment and clinical/cognitive outcome assessment. Blood biomarker, advanced MRI and outcome assessment will be repeated face to face at 6 and 12 months after injury.

Work package 3 involves the addition of cerebral microdialysis assessments acutely during the inpatient admission. Blood biomarker assessment is more frequent, up to twice per 24 hours period during cerebral microdialysis. Standard MRI is performed alongside blood biomarkers at 10 days to 6 weeks. Face-to-face outcome assessments are performed at 6 and 12 months postinjury.

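### Change in blood biomarkers, a primary outcome, is to be analysed with paired tests chosen after a normality check; a mixed model on log concentration with actual day since injury fits the design better

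*Protocol article*

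**What the plan says.** In the protocol article, the Sample size section lists "Change in levels of fluid biomarkers in blood" as the third of four primary outcome measures, with "time frame: 0–5 days, 5–10 days, 10 days to 6 weeks, 6 months and 12 months". The same section assumes 25%–30% loss to follow-up and aims to enrol 250 patients.

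The Fluid biomarkers part of the Statistical analysis plan gives the method. "Distributions of variables will be assessed for normality", and then "parametric/non-parametric tests used as needed for comparisons, with paired tests used within subjects for repeated measures". Linear and logistic regression are named only for relating biomarker levels to outcomes.

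Structure of assessments gives the sampling schedule. In work package 1, "Blood samples will be collected twice in the first 10 days after injury"; later samples are due at the visit between 10 days and 6 weeks and at about 12 months. Blood at 6 months is listed only for work package 2, which Table 2 assigns to three of the eight centres. For work package 3 no blood is listed after 10 days to 6 weeks.

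The objectives for work package 1 include describing the time course of plasma biomarkers, with NFL and tau named.

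**The concern.** A paired test compares one window with another as if every sample in a window had been drawn at the same time, and it needs both values. Neither property suits this design.

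- **Timing.** One window runs from day 10 to 6 weeks. If levels move over that period, the paired difference mixes biological change with the accident of when each patient was sampled. The time course that work package 1 aims to describe is then reduced to differences between windows.
- **Incomplete pairs.** Patients without the later sample contribute nothing, even when their early levels are known. If patients with high early levels are the ones lost, the remaining pairs give a distorted mean change.
- **Changing sets.** Because 6-month blood comes from work package 2 only, different contrasts rest on different patients and centres.
- **Test chosen from the data.** Deciding between a parametric and a rank-based test after a normality check lets the data decide whether a mean change or a rank-based shift is estimated. Fixing the log scale in advance avoids this.

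**Working it through.** The article gives no effect size, SD or power for biomarker change, so there is no stated figure to reproduce. The inputs from the document are the windows (5, 5 and 32 days wide for the first three), 250 patients and 25%–30% loss. Slopes, SDs, correlations and dropout models below are assumptions, shown as ranges.

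**1. Complete pairs to 12 months.** 250 × 0.75 = 187.5 and 250 × 0.70 = 175. So about 62–75 patients with early values only would drop out of a paired test. This counts every patient as scheduled for 12-month blood, so it is an upper figure for the pairs.

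**2. Bias from incomplete pairs.** Take two visits, log concentration with SD 1 at each, and correlation ρ. If loss depends on the early level and lowers the early mean of the retained patients by d, their later mean is lowered by ρd. The paired change is then off by d − ρd = (1 − ρ)d. Simulation (2,000 runs per setting, 250 patients, true change −0.50, loss more likely with a higher early level) gave:

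| ρ | Loss | Log-odds of loss per SD | Paired change | Likelihood estimate | Coverage of paired 95% CI |
|---|---|---|---|---|---|
| 0.3 | 25% | 0 | −0.498 | −0.499 | 96% |
| 0.3 | 25% | 0.5 | −0.418 | −0.501 | 84% |
| 0.3 | 30% | 1.0 | −0.324 | −0.500 | 48% |
| 0.6 | 25% | 0 | −0.499 | −0.499 | 95% |
| 0.6 | 25% | 0.5 | −0.452 | −0.500 | 88% |
| 0.6 | 30% | 1.0 | −0.399 | −0.500 | 66% |

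The likelihood estimate is what an unstructured mixed model gives for this pattern. Where loss depends on level, the paired bias runs from 0.50 − 0.452 = 0.048 to 0.50 − 0.324 = 0.176, or about 0.05–0.18 log units. The formula agrees. In the 30% loss, log-odds 1.0 rows, 0.176/0.7 and 0.101/0.4 both give d = 0.25.

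With 29% loss and ρ = 0.6, a bias of +0.07 SD units corresponds to d = 0.07/0.4 = 0.175. If loss depends on the second visit and all correlations are equal, the first visit and the 12-month visit are both lowered by ρd. The paired change between those two is then unbiased. The bias is therefore tied to the visit that drives loss.

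**3. Precision when loss is unrelated to level.** At 25% loss the paired and likelihood SEs are 0.085 and 0.082 (ρ = 0.3), and 0.064 and 0.063 (ρ = 0.6). The ratios are 1.04 and 1.02. At 30% loss they are 0.090/0.085 = 1.06 and 0.067/0.065 = 1.03.

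**4. Timing noise.** With sampling day uniform in windows of width w₁ and w₂, and log slope s per day, the variance added to a paired change is s²(w₁² + w₂²)/12. The width terms are (25 + 25)/12 = 4.17 for 0–5 against 5–10 days, and (25 + 1024)/12 = 87.4 for 5–10 days against 10 days to 6 weeks. The table shows the factor by which the variance of the change is multiplied, for an SD of change of 0.8 and of 0.4.

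| s per day | 0–5 v 5–10 days | 5–10 days v 10 days–6 weeks |
|---|---|---|
| 0.02 | 1.00, 1.01 | 1.05, 1.22 |
| 0.05 | 1.02, 1.07 | 1.34, 2.37 |
| 0.10 | 1.07, 1.26 | 2.37, 6.46 |

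The last row is an extreme: 0.10 per day sustained for 32 days is 3.2 log units, about a 25-fold change.

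**5. Unequal timing between groups.** If two groups differ by 2 days in their sampling gap, slopes of 0.05–0.20 per day give a spurious ratio of exp(0.10) = 1.11 to exp(0.40) = 1.49.

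**The case against.** The strongest reply is that this is a brief summary in a journal article. It does not say that sampling day will be ignored or incomplete pairs discarded, and a full analysis plan may add covariates, a transformation and missing-data methods. Biomarker change is also largely descriptive here, and the study is powered on DTI and atrophy. The first part stands as a limit: those two consequences are inferred from the named test, not written. But the article does name the test for a primary outcome, so the choice itself is open to review.

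Several stronger readings are tempting and not supported:

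- **That the 5–10 day window will be left empty, or that the schedule contradicts the outcome.** Two samples in 10 days and windows of 0–5 and 5–10 days can be read together as one sample in each. The wording permits two samples in one window but does not plan it.
- **That a mixed model would recover the precision lost to dropout.** It cannot replace samples never taken, and the like-for-like gain is small.
- **That acute sampling day adds large noise.** This needs a short plasma half-life, and the document gives none. Its remark that "brain extracellular levels of NFL remain elevated for a longer period than tau and show heterogeneous dynamics" concerns brain extracellular fluid, not plasma.
- **That the missing 6-month sample in work package 1 causes loss bias.** It is missing by centre design. It limits who informs that contrast but is not outcome-driven dropout.
- **That sicker patients are sampled earlier or later.** The document does not say so. It is a risk, with no stated direction.

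**Conclusion.** The concern holds as a weakness in a stated method, not as an error that invalidates the study. For a primary outcome measured over unequal and sometimes wide windows, with expected loss and planned gaps, paired tests chosen after a normality check are a poor primary analysis.

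The size depends on assumptions. If loss depends on the early level (log-odds 0.5–1.0 per SD, correlation 0.3–0.6, 25%–30% loss), the paired change is biased by about 0.05–0.18 log units and its 95% interval covers 48%–88%. Under loss of patients with high early levels, as assumed here, a fall is understated; the opposite pattern would reverse the sign. If loss is unrelated to level, there is no bias and little precision at stake. Timing is a minor issue between the two acute windows and could be a major one for 10 days to 6 weeks, depending on how fast levels change.

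A reader might infer that the paired results must be biased. The documents do not support that, because they do not say how loss relates to biomarker level.

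**What to change.** - Make the primary analysis of biomarker change a linear mixed model of log concentration on actual days since injury, entered flexibly (for example as a spline). Include random patient effects, age, sex and centre, and use all available samples.
- Report change as model contrasts at fixed days, and keep the paired tests as sensitivity analyses.
- Include sampling day in the regressions that relate biomarker levels to outcome.
- State in Structure of assessments and in Blood biomarkers that the two acute samples are one in each of the 0–5 and 5–10 day windows given in the Sample size section.

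The cost is plan wording and modest analysis work, with no extra patients or samples. It needs the date of each sample. The article does not state that this is recorded, but windows defined by days since injury imply it. The model is unbiased only if data are missing at random given what was observed. That assumption should be stated, and deaths need separate handling.

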## Goals and objectives of BIOmarkers of AXonal injury after TBI

### Acute injury measures and relationship to clinical outcome (work package 1)

We aim to identify the most informative plasma biomarker(s) of the severity of axonal injury using a large multicentre cohort of adult moderate-to-severe patients with TBI. We will characterise their time course focusing on NFL and tau, and relate these to MRI measures of axonal injury in the early phase postinjury. We will assess how these measures contribute to the prediction of clinical, cognitive and functional outcome at 12 months.

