### Validation in large cohort and CT head neuroimaging analysis (work package 4)

The outputs of the above will be used to select the plasma biomarkers of axonal injury that best predict clinical outcome. These biomarkers will be validated by exploiting a large sample (~n=1000) of patients with TBI collected within the CREACTIVE project. In addition, the relationship between the CT head scan appearances and plasma biomarkers will be investigated using machine learning analysis to test whether CT head scans contain specific features of axonal injury and whether these features can be used to help predict outcome.

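### Binarising GOSE at either 6 or 12 months discards ordinal information, leaves open a time point that the objective fixes, and states no test of added prediction

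*Protocol article*

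**What the plan says.** The work package 1 objective reads: "We will assess how these measures contribute to the prediction of clinical, cognitive and functional outcome at 12 months". Work package 4 then uses the results to "select the plasma biomarkers of axonal injury that best predict clinical outcome", and validates those markers in about 1000 CREACTIVE patients. The Sample size section states that "a minimum of 140 patients will be necessary to test the contribution of DTI to prognostic modelling", with the design values given as "type 1 error=0.05, power=0.95". It gives the biomarkers no calculation of their own and expects that the numbers for comparing groups and for "relationships to outcome will be smaller than for DTI (1) or brain atrophy rates (2), on whose measures the study is primarily powered".

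The Fluid biomarkers part of the statistical analysis plan gives two models. The first is worded as follows: "We will use linear regression to look at the relationship between blood biomarker levels and continuous outcomes". The second, and the only one that names GOSE, is "logistic regression for binarised outcomes such favourable/unfavourable recovery on the Glasgow Outcome Scale-Extended (GOSE) at 6 or 12 months". The section does not define the favourable/unfavourable cut, choose between the two times, or mention a comparator model.

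Table 3 schedules GOSE at 10 days to 6 weeks, 6 months and 12 months in all three patient work packages. Under Structure of assessments, the 6-month assessment is by telephone in work package 1 and face to face in work packages 2 and 3. At 12 months it is face to face in all three; for work package 1 the article adds a remote fallback. Table 2 assigns each site to one work package.

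**The concern.** Three features of the stated analysis fit the objective poorly.

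- **Scale.** GOSE is an ordered eight-level outcome, and the only analysis named for it uses two levels. Differences within the favourable and unfavourable halves contribute nothing.
- **Time.** The objective fixes 12 months and the analysis does not. If both times are run and the more striking one is reported, the nominal 5% no longer holds. Because work package goes with site, assessment mode at 6 months is confounded with centre.
- **Question.** Contribution to prediction asks what a marker adds to what is already known about the patient. A regression of outcome on marker level, as worded, shows association. A marker can be associated with outcome because it tracks injury severity, and add little beyond it.

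At stake are power for the clinical outcome and the choice of markers carried forward to the CREACTIVE validation.

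**Working it through.** **1. The plan's own figure.** The 140 cannot be reproduced, because no effect size, number of predictors or outcome is given. Working back with two-sided alpha 0.05 (the sidedness is assumed) and power 0.95, z = 1.960 + 1.645 = 3.605. For a single correlation, r = tanh(3.605/√137) = 0.30. For one added predictor in a linear model, the noncentral F test gives f² = 0.094. For a binary outcome, the odds ratio per SD is exp(3.605/√(140·p(1−p))), which is 1.84 at 50:50 and 2.14 at 80:20. The plan says that it "allowed for up to a further 25%–30% lost to follow-up by aiming to enrol 250 patients". That leaves 250 × 0.70 = 175 to 250 × 0.75 = 187.5 evaluable, above 140.

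**2. Information lost by cutting GOSE.** Under proportional odds and near the null, the efficiency of a binary cut relative to the full scale is RE = 3p(1−p)/(1 − Σp_k³). Here p is the proportion favourable (taken as GOSE 5 to 8) and p_k are the eight category proportions. The article gives neither the cut nor the distribution, so all rows are assumptions.

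| Assumed distribution, GOSE 1 to 8 (%) | p | 3p(1−p) | 1 − Σp_k³ | RE | Loss |
|---|---|---|---|---|---|
| 22, 2, 18, 8, 13, 12, 13, 12 | 0.50 | 0.750 | 0.975 | 0.769 | 23% |
| uniform, 12.5 each | 0.50 | 0.750 | 0.984 | 0.762 | 24% |
| 35, 3, 22, 8, 10, 8, 8, 6 | 0.32 | 0.653 | 0.944 | 0.692 | 31% |
| 10, 1, 12, 7, 15, 17, 20, 18 | 0.70 | 0.630 | 0.975 | 0.646 | 35% |
| 5, 1, 7, 5, 12, 18, 25, 27 | 0.82 | 0.443 | 0.957 | 0.463 | 54% |

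With 175 evaluable patients, the binary analysis is worth 175 × 0.769 = 135 patients analysed ordinally at the top of the table and 175 × 0.463 = 81 at the bottom.

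**3. What that could mean for power.** Suppose the 0.95 at n = 140 referred to the full scale, which the article does not say. Power after binarising is Φ(3.605·√(1−loss) − 1.960): 0.88 at 24% loss, 0.86 at 30% and 0.72 at 50%. The n needed to restore 0.95 is 140/(1−loss): 185, 200 and 280.

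**4. Open time point.** Take two two-sided 5% tests on bivariate normal statistics with correlation ρ. The chance that at least one is significant under the null is 8.8% at ρ = 0.6, 7.8% at ρ = 0.8 and 7.0% at ρ = 0.9. The correlation is assumed, and the inflation occurs only if the better result is chosen.

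**5. Association against added value.** The partial correlation of marker and outcome given a clinical score is (r_my − r_ms·r_sy)/√((1−r_ms²)(1−r_sy²)). Take r_my = 0.30 from step 1 and assume r_sy = 0.6 between score and outcome.

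- r_ms = 0.5: (0.30 − 0.30)/√(0.75 × 0.64) = 0
- r_ms = 0.3: (0.30 − 0.18)/√(0.91 × 0.64) = 0.16
- r_ms = 0.1: (0.30 − 0.06)/√(0.99 × 0.64) = 0.30

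The same association is compatible with no added value or with full added value. The document gives none of these correlations, so this shows only that the two questions differ.

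**The case against.** The strongest reply is that much of this rests on a condensed article.

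- **Covariates.** A reader might infer that the models contain the biomarker alone. The article does not say so; it is silent on covariates, and these may be set in the full protocol or analysis plan. The reference in Sample size to prognostic modelling suggests that other terms are intended. This stands.
- **Model class.** A reader might also infer that these regressions cannot show added prediction. They can, once nested models are compared. The fair statement is that no such comparison is described here. This stands.
- **Weight of GOSE.** Binarised GOSE is given as an example beside linear regression of continuous outcomes, and GOSE is not one of the four listed primary outcome measures. The prognostic question therefore does not hang on it alone. This stands and limits the weight of the point.
- **Size of the loss.** At an even split the loss is about 23% to 24%, and no document figure fixes the distribution. The favourable/unfavourable split is also clinically interpretable, so binarising is a choice and not an error. This stands, but the loss is material across the whole assumed range.
- **Numbers.** Recruitment had reached 311 by June 2020. At 25% to 30% loss that leaves about 218 to 233 evaluable patients, more than the 175 used above. This softens the power consequence but does not change the relative efficiency.
- **Time point.** Naming both times may mean a model at each visit, and CREACTIVE validation gives some protection against a chance finding. The mode difference concerns 6 months only, and nothing in the article shows that mode shifts GOSE. This stands in part: the wording still does not say which time answers the 12-month objective.

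**Conclusion.** The point holds as a cheap improvement to the analysis, not as a flaw that invalidates the study. Two parts rest on stated text. GOSE is binarised, at a cost of roughly 23% to 54% of the information relative to proportional odds (assumed distributions, cut at 4/5). The time is left as 6 or 12 months although the objective names 12, with about 7% to 9% false positives if the better result is taken (assumed correlation 0.6 to 0.9). The third part is narrower: as worded, the regressions describe association and state no test of contribution to prediction, and the full protocol or analysis plan may supply one. The power figures and partial correlations are illustrations under assumptions, not estimates for this study.

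**What to change.** In the Fluid biomarkers part of the statistical analysis plan:

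1. Name GOSE at 12 months as the main clinical outcome for the prognostic analysis, matching the work package 1 objective.
2. Analyse all its levels by proportional-odds regression. Keep the favourable/unfavourable logistic analysis, with its cut defined, and the 6-month analysis as secondary.
3. For each marker, compare a base model with base plus marker. The base model would use predictors already collected, such as age, lowest GCS, CT findings and centre. Report the likelihood-ratio test and the optimism-corrected change in c-index or R². If the full protocol or analysis plan already sets this out, a sentence referring to it is enough.

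No new data are needed. The cost is revised wording, a proportional-odds assumption to check, and slightly more analysis work. The binary result remains available if that assumption fails.
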